##### Muscle Synergies

Muscle synergies will be identified via electromyographic (EMG) recordings from 4 muscles involved in wrist flexion, extension, and radial or ulnar deviation, and selected for their accessibility to EMG recordings, superficial anatomical location, and distinct activation patterns during wrist movements. The *flexor carpi radialis* (FCR) was selected for its role in wrist flexion and radial deviation, with increased activation expected during supination and radial deviation. The FCR is located superficially on the anterior forearm, medial to the brachioradialis. Electrodes will be positioned one-third of the distance from the medial epicondyle of the elbow to the wrist crease, and just lateral (radial side) to the palmaris longus tendon (if present), with an interelectrode distance of 2 cm more distal [37]. The *flexor carpi ulnaris* (FCU), contributing to wrist flexion and ulnar deviation, will also be included. The FCU will be located along the ulnar border of the anterior forearm, adjacent to the ulna, with electrodes placed at one-third of the forearm length from the wrist, following the muscle’s longitudinal axis, with an interelectrode distance of 2 cm more distal [38]. For wrist extension, the ECRB will be targeted for its primary role in wrist extension and radial deviation. The ECRB will be located 1 cm lateral to a point that is 5 cm distal to the lateral epicondyle, along a line connecting the lateral epicondyle to the midline of the wrist, with an interelectrode distance of 2 cm more distal, to minimize muscle activity cross-contamination from adjacent muscles such as the extensor carpi radialis longus and the brachioradialis [39]. Finally, the *extensor carpi ulnaris* (ECU) will be selected for its contribution to wrist extension and ulnar deviation. Electrodes will be placed on the dorsal ulnar forearm, one-third of the way down the forearm from the lateral epicondyle (elbow) toward the wrist, on the ulnar (medial) side, and aligned with the muscle belly, with an interelectrode distance of 2 cm more distal [40,41]. A ground electrode will be placed over the olecranon. Every electrode will be placed on lightly abraded skin using Nuprep Skin Prep Gel (Weaver and Company) and alcohol. Each electrode will be placed according to the guidelines established by Hermens et al [42].

Every EMG signal will be collected using 24-mm diameter adhesive clipped disposable wired Ag/AgCl surface electrodes (Kendall H124SG), amplified (×1000), band-pass filtered (20‐1000 Hz) using a NeuroLog module NL125/NL126 (Digitimer), sampled at a rate of 5 kHz with a CED Micro 1401 mk II acquisition system, and recorded in CED Signal v6.0 software (Cambridge Electronic Design Limited).

EMG signals from the FCR, FCU, ECRB, and ECU muscles will be preprocessed using a customized MATLAB algorithm. The linear trend will be removed before filtering each signal with a fourth-order zero-lag band-pass Butterworth filter set between 20 Hz and 1000 Hz to remove motion artifacts at low frequencies and high-frequency noise. Full-wave rectification and smoothing through a fourth-order zero-lag low-pass Butterworth filter (cutoff frequency 5 Hz) will then yield EMG envelopes. Each muscle EMG envelope will subsequently be normalized by its peak activation observed across the whole visit, ensuring that synergy extraction reflects relative muscle coordination patterns independently of absolute activation magnitude. This normalization minimizes the influence of between-visit amplitude variability due to electrode placement, skin impedance, and amplifier gain, which are known to produce substantial day-to-day variability and can confound interpretation of activation amplitude [43-45]. This type of within-session peak normalization is commonly used when the focus is on coordination patterns and synergy structure, rather than on absolute activation levels [46,47]. Envelopes will then be cut using segmentation time stamps from kinematic data, and each of the 16 individual movements will be time-normalized to *t*=3000 samples. Individual movements will then be concatenated to represent the whole visit (6 turns) as a single data matrix. Spatial muscle synergies will be assessed each visit (*v*=4) from concatenated EMG envelopes by the nonnegative matrix factorization (NNMF) approach [48], as implemented in MATLAB (alternating least squares algorithm). The model will thus include for each participant and each visit the *m*=4 muscles (FCR, FCU, ECRB, and ECU) and all repeated (*r*=6) round trips corresponding to 16 pointing tasks (*k*=16). The NNMF approach can extract muscle synergies, *s* ranging from 1 to *m*–1=3. The spatial synergy (*U*, with *m* rows and *s* columns) and temporal coefficients (*C*, with *s* rows and *k × r × t* columns) will be identified from the preprocessed EMG matrix *M* (equation 1). This optimization will run 20 times to ensure the lowest possible reconstruction error (ε, with *m* rows and *k× r × t* columns; equation 1) since the NNMF method iterates from a random seed.

(1)
M=U⋅C+ε

The reconstructed EMG matrix (equation 2) will be used to assess reconstruction quality using the variance accounted for (VAF) (equation 3). Unlike a coefficient of determination, the total sum of squares is not centered. VAF will be computed both globally and for each individual muscle (by setting the chosen muscle index and removing the summations over muscles in equation 3). A total of 20 VAF values will thus be associated with each participant [(*m* + 1) × *v*]. The minimal number of synergies required to reach satisfactory reconstruction quality will be optimized individually for each visit according to a threshold of 0.8 for each of the 5 associated VAF values (*m* individual muscle values plus global VAF).

(2)
$$\hat{M}=U\cdot C$$

(3)
$$VAF=1-\frac{\sum_{muscle=1}^{2}\sum_{time=1}^{t}{\left(M_{muscle,time}-{\hat{M}}_{muscle,time}\right)}^{2}}{\sum_{muscle=1}^{2}\sum_{time=1}^{t}M_{muscle,time}^{2}}$$

Synergy variability will involve only synergy activation variability since no motor adaptation should occur within 1 visit (no muscle synergy composition variability). The variability of activation coefficients will be quantified by the Pearson correlation coefficient (*r*), the maximum value of the normalized cross-correlation coefficient (*r*_max_), and the time shift between activation curves (lag_%_, expressed as a percentage of movement duration) between turns. All 3 variability metrics for each muscle synergy will be averaged across all pairwise combinations of the same 16 individual movements within a visit. *r, r*_max_, and lag_%_ values will finally be averaged over muscle synergies to reflect overall synergy activation variability. High muscle activation variability is reflected by low *r* and *r*_max_ values, as well as larger time shifts lag_%_. This approach is inspired by work based on the similarity of muscle synergy [49], although referring to activation similarity instead of activation variability. Metrics on intravisit muscle synergy activation variability (*r, r*_max_*,* lag_%_) will be compared between pain-free and pain-induced conditions regardless of muscle synergy composition between pain conditions.

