### Data Collection Procedures

#### Primary Outcomes: Motor Behavior

##### Overview

Although a predefined preprocessing pipeline will be applied, data-driven adjustments may be performed when warranted by data quality, statistical assumptions, or artifact structure. Every adjustment will be reported in the final study. Multidimensional movement tasks will be performed to assess both kinematic and muscle synergy variability. Participants will be seated on an adjustable seat with their right forearm resting on a table in neutral pronation-supination with approximately 70° of shoulder abduction. Their wrist will be positioned at the edge of the table with their hand extending beyond it, allowing the forearm to be supported without hindering wrist mobility. The task involves executing multidimensional wrist movements toward 9 white round targets (4.5 cm in diameter), 1 central and 8 peripheral, arranged in a circular configuration, separated by 45° from the central target, at a 1-meter distance on a black fabric wall. The 8 peripheral targets will be separated from the central one according to the functional ranges of motion of the wrist joint [28-31]. The targets will be arranged at 40° flexion (50% of the average amplitude of approximately 80°), or 84 cm below the central target; at 40° extension (57% of the average amplitude of approximately 70°), or 84 cm above the central target; at 15° radial inclination or abduction (75% of the average amplitude approximately 20°), or 27 cm to the left of the central target; and at 20° ulnar inclination or adduction (67% of the average amplitude approximately 30°), or 36 cm to the right of the central target. A green laser pointer, mounted on the dorsal surface of the right hand via an adjustable glove and aligned with the middle finger, will project a laser dot to indicate movement direction to participants. Participants will move the right wrist, keeping the elbow and forearm fixed by hook-and-loop fasteners on the table, to guide the laser pointer from the central target to each peripheral target and then returning to the central target (Figure 2). Movements will be performed in both clockwise and counterclockwise directions, alternating between the two. Each direction will be repeated 3 times, resulting in a total of 6 complete tours. Each tour consists of 16 movements, or 8 round trips from the central target to the 8 peripheral targets, with brief pauses between sequences. The task will follow a metronome cadence of 90 beats per minute, resulting in a total of 96 movements completed in 1 minute and 4 seconds, excluding pauses. Participants will be instructed to prioritize accuracy, aiming the laser pointer precisely at the targets and avoiding any corrective adjustments once a target has been reached. To establish a stable baseline for task performance, participants will undergo a separate familiarization time for all visits, just before the actual task. During this time, they will practice the task until they achieve a performance plateau, defined as a movement accuracy exceeding 95%. Previous research has demonstrated that 3 complete tours (or 48 trials) are sufficient to reach this plateau and that movement accuracy remains stable over several days [32]. Kinematic data will be recorded using a 3D Optotrak motion capture system (Northern Digital Inc) at a sampling frequency of 100 Hz tracking 3 infrared light-emitting diodes bound to the glove on the back of the right hand, roughly matching the distal end of the second and fifth metacarpal bones. Data will be processed by a customized Python (Python Software Foundation) script.

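### Equation 3 (VAF) prints summation limits of 2 muscles and t samples, which contradict the 4-muscle, whole-visit matrix defined in the same section; this is probably a notation error, but it sits in the formula behind the 0.8 synergy rule

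*Protocol article*

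**What the plan says.** All of this is in the protocol article, Methods, Muscle Synergies, unless stated otherwise.

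- **Muscles:** "The model will thus include for each participant and each visit the *m*=4 muscles (FCR, FCU, ECRB, and ECU").
- **Length of one movement:** "each of the 16 individual movements will be time-normalized to *t*=3000 samples". The symbol t therefore belongs to a single movement.
- **Repetition:** "all repeated (*r*=6) round trips corresponding to 16 pointing tasks (*k*=16").
- **Matrix to be factorised:** "Individual movements will then be concatenated to represent the whole visit (6 turns) as a single data matrix". The temporal coefficients and the residual are both given k x r x t columns, and the residual m rows.
- **Equation 3:** the sums run over "muscle=1}^{2}\sum_{time=1}^{t", that is, muscle 1 to 2 and time 1 to t, in the numerator and again in the denominator.
- **Per-muscle VAF:** obtained from equation 3 by fixing the muscle and dropping the muscle sum, so it keeps the printed time limit.
- **Use:** the smallest adequate number of synergies is chosen for each visit "according to a threshold of 0.8 for each of the 5 associated VAF values". The five are one value per muscle plus the global one, and the text counts 20 VAF values per participant as (m + 1) x v with v = 4 visits.

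**The concern.** The equation is a working formula. It is the only place where the article defines the statistic behind the 0.8 rule, and that rule fixes how many synergies are retained at each visit. The activation-variability metrics (r, r_max and lag) are then averaged over the retained synergies. They form the muscle-synergy part of the primary outcome, for which the Statistical Analysis section plans one of its two models.

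As printed, the formula would stop after two muscles and after the samples of one movement. The per-muscle values inherit the time limit, and no other sentence restates the time range for VAF. The Dissemination Plan promises that scripts and pipelines will be deposited, so readers will be able to compare the code with this equation. Enrolment has begun (26 participants by April 2026, Results, Overview), so some visits may already have been processed.

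**Working it through.** **Inputs.** m = 4, k = 16, r = 6, t = 3000 and v = 4 (Muscle Synergies); 96 movements at 90 beats per minute (Primary Outcomes, Overview).

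**Step 1: reproduce the article's own counts.**
- Movements per visit: k x r = 16 x 6 = 96. At 90 per minute this takes 96 / 90 x 60 = 64 s, which agrees with "resulting in a total of 96 movements completed in 1 minute and 4 seconds, excluding pauses".
- VAF values per participant: (m + 1) x v = (4 + 1) x 4 = 20, as stated. With two muscles the count would be (2 + 1) x 4 = 12, so the prose works with four muscles.
- The same count allows five VAF values per visit. One set per movement would give 5 x 96 x 4 = 1,920 values. The prose therefore treats the visit, not the movement, as the unit.

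**Step 2: size of the matrix.**
- Columns: k x r x t = 16 x 6 x 3000 = 288,000.
- Cells: m x k x r x t = 4 x 288,000 = 1,152,000.

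**Step 3: coverage if equation 3 is coded as printed.**
- Each per-muscle VAF: 3,000 / 288,000 = 1.04% of that muscle's samples.
- Global VAF: 2 x 3,000 = 6,000 cells; 6,000 / 1,152,000 = 0.52%.
- All five values together: 4 x 3,000 = 12,000 cells; 12,000 / 1,152,000 = 1.04%.
- Muscle limit wrong but time limit right: the global VAF covers 2 / 4 = 50% of the cells.

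**Step 4: which limit can affect the 0.8 rule.** Write SS_i for the uncentred sum of squares of muscle i. Then global VAF = sum of w_i x VAF_i, with w_i = SS_i / sum of SS_i. The weights are non-negative and add to 1, so the global value is a weighted mean of the per-muscle values. If all four per-muscle VAFs are at least 0.8, the global value is at least 0.8 whether it is taken over two muscles or four. The rule already requires all four, so the muscle limit cannot change the number of synergies chosen. The time limit can, because it changes the per-muscle values themselves.

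**Step 5: illustration only.** In 150 simulated visits (three true synergies, burst-shaped activations, assumed amplitude variation and noise, movements shortened to 30 samples), the muscle limit alone changed the chosen number in 0 of 150. Applying both printed limits changed it in 81 of 150. The first result follows from step 4. The second depends on the assumed signals and noise, which the article does not give, and is no estimate for this trial.

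**Step 6: after correction.** With muscle = 1 to m and time = 1 to k x r x t, the global VAF covers all 1,152,000 cells and each per-muscle VAF all 288,000 samples of its muscle.

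**The case against.** The strongest reply is that nobody would read the plan this way. The visit is concatenated into one matrix, the reconstructed matrix is the full product U x C, and the 20 VAF values need four muscles. On that view t in equation 3 is loose notation for the last sample, and the 2 is a slip. A programmer would have to cut a full-matrix calculation deliberately to its first 3000 columns, and nothing suggests that this was done. This stands as to intent, and it is why the point is put as a probable notation error. It does not make the equation right: t is defined in the same section as the length of one movement, and the section writes k x r x t when it means the visit.

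Three stronger readings are tempting, and the article does not support them.

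- *The 0.8 rule is applied to about 1% of the data.* That treats the misprint as the plan. The prose points to the full matrix, and the code is not shown.
- *The injected ECRB escapes the quality check.* It keeps its own VAF and its own 0.8 threshold. The two-muscle limit touches only the global value, and since no row order is stated, which two muscles it would cover can only be guessed from the listing order.
- *The synergy outcome is distorted.* Only the coverage shares follow from the document. How often the chosen number would change, and how far r, r_max or lag would move, depends on signals that are not given.

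**Conclusion.** The contradiction is certain: both upper limits in equation 3 disagree with the definitions in its own section. An extraction fault is unlikely, since the same limits appear intact in both numerator and denominator. Because the article prints the formula, this is a stated error and not a detail left to another document.

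Its effect is conditional. If the script follows the prose, nothing in the results changes and only the equation needs correcting. If the script follows the print, the shares in step 3 apply: the reported global VAF would be wrong, and the number of synergies could be wrong through the time limit alone. The document cannot show which is the case. The point merits correction because the formula governs a decision rule for a primary outcome and the remedy is cheap; it is not evidence that the synergy analysis is compromised.

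**What to change.** - Rewrite equation 3 with muscle = 1 to m (m = 4) and time = 1 to k x r x t (288,000), in both numerator and denominator.
- State that the per-muscle VAFs use the same time range.
- Confirm that the MATLAB script sums over these limits, and recompute processed visits only if it does not.

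The cost is one corrected equation, one added sentence and a short code check. No new data are needed, and any rerun would be confined to visits already processed.

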### Cortical Mechanisms

#### Peak Alpha Frequency

Electroencephalographic (EEG) sensorimotor PAF will be recorded while the participants are comfortably seated. Scalp EEG will be recorded using the Brain Products platform (BrainVision Recorder, v1.22.0101 with actiCHamp Plus, Brain Products GmbH) at a sampling rate of 5000 Hz. Signals will be recorded from 63 active electrodes (actiCAP slim, Brain Products GmbH), embedded in an elastic cap (EASYCAP, EASYCAP GmbH) in line with the 10‐10 system [50]. Recordings will be referenced online to “FCz” with the ground electrode placed on “FPz.” Electrode impedances will be maintained below 5 kΩ during setup [51]. Once setup is complete, the lights will be switched off with ambient noise reduced to a minimum. Participants will be instructed to relax their muscles and keep their eyes closed while remaining awake. The resting-state EEG signal will then be recorded for 5 minutes.

EEG data processing will be conducted using custom MATLAB scripts implementing the EEGLAB (eeglab2025.0.0) and FieldTrip (fieldtrip-20251201) toolboxes [52]. The preprocessing pipeline will consist of data downsampled to 500 Hz, rereferenced from the online FCz reference to common average, band-pass filtered between 2 and 100 Hz with a notch filter at 60 Hz using a finite impulse response filter, and removal of auxiliary channels (galvanic skin response, heart rate, and respiration). A 5-minute resting-state window will be extracted. Channel data will be visually inspected in both time and frequency domains using spectral plots, and overtly noisy channels will be removed before rereferencing. Data will be segmented into 5-second epochs with no overlap (60 epochs total), and epochs containing marked artifacts will be manually rejected using FieldTrip’s visual rejection tool (±100 µV amplitude threshold). Independent component analysis will be applied using the runica method with 20 principal components retained. Components will be visually inspected via topographic maps, time-course plots, and frequency spectra to identify components with a clear alpha peak (8‐12 Hz) and scalp topography suggestive of sensorimotor cortex sources (bilateral distribution over central regions). Missing channels will be interpolated using the spline method with neighboring electrode templates prior to frequency decomposition. Mastoid electrodes (M1/M2) will be excluded from interpolation and final analysis. The power spectral density of the chosen sensorimotor component will be derived in 0.2 Hz bins across the 2‐50 Hz range using multitaper Fast Fourier Transform with a Hanning taper to reduce edge artifacts using the formula (equation 4). PAF will be calculated as the center of gravity (power-weighted mean frequency) within the 8‐12 Hz window, with equation 5.

(4)
PAF=∑(f×P(f))/∑(P(f))

(5)
$$CoG=\frac{\sum_{i=1}^{n}f_{i}\;a_{i}}{\sum_{i=1}^{n}a_{i}}$$

#### TMS Corticomotor Excitability

##### Overview

Motor-evoked potentials (MEPs) will be recorded from the right ECRB using wired Ag/AgCl clipped disposable adhesive 24-mm diameter surface electrodes (Kendall H124SG) and a TMS device (BiStim² and 200, Magstim Company Ltd) equipped with a figure-of-eight coil (P/N9925-00 S/N2349) outer diameter 90 mm. The signals will be amplified (×1000) and band-pass filtered (20‐1000 Hz) using a NeuroLog module NL125/NL126 (Digitimer), sampled at a rate of 5 kHz with a CED Micro 1401 mk II acquisition system and recorded in CED Signal v6.0 software (Cambridge Electronic Design Limited). The ECRB is a forearm muscle responsible for wrist extension and abduction, originating from the lateral epicondyle of the humerus and inserting at the base of the third metacarpal bone. Surface EMG electrodes will be positioned 1 cm lateral to a point that is 5 cm distal to the lateral epicondyle, along a line connecting the lateral epicondyle to the midline of the wrist, with an interelectrode distance of approximately 20 mm more distal, to minimize cross-contamination from adjacent muscle activity such as from the extensor carpi radialis longus and the brachioradialis [42,53,54]. The ground electrode will be placed on the olecranon to ensure minimal interference with the EMG signals. Before each application of EMG electrode, the skin will be lightly abraded using *Nuprep* skin prep gel (Weaver and Company) and then cleaned with alcohol.

To locate the optimal spot (hotspot) for the right ECRB muscle, the participant will be positioned comfortably with their forearm supported and relaxed. The coil will be used to initiate stimulation over the left M1, approximately 5 cm lateral from the vertex (Cz). To localize the Cz, the nasion-inion and interaural distances will be measured along the midline using a flexible measuring tape. The midpoint of each measurement will be marked, and their intersection will define Cz [55]. The coil will be systematically moved in 1-cm increments around this area, delivering 2‐3 stimuli at each location. The coil position that consistently elicits the largest MEPs, at the lowest stimulator intensity, in the ECRB will be identified as the hotspot. This location will be marked using a neuronavigation display system (Brainsight, Rogue Research Inc) to ensure reproducibility. Once the hotspot is determined and recorded in the neuronavigation system, the resting motor threshold (rMT) will be established using Motor Threshold Assessment Tool 2.0 software. Motor Threshold Assessment Tool 2.0 will use an automated procedure using a maximum likelihood parametric estimation by sequential testing algorithm [56] and will adjust stimulation intensities and prompt for input on whether an MEP ≥50 μV was observed after each pulse [57]. The final rMT will be defined as the lowest stimulation intensity that reliably elicits MEPs ≥50 μV in at least 50% of trials with 95% confidence.

